## Methodology

### Study aims

The primary aim of this study is to compare absolute weight change among participants receiving daily healthy meals or produce box versus matched controls (standard of care) at 16 weeks from baseline:This aim tests the hypothesis that receiving daily healthy meals will result in greater absolute weight loss compared to receiving a produce box or standard of care at 16 weeks from baseline.This aim tests the hypothesis that receiving either daily healthy meals or a produce box will result in greater absolute weight loss compared to standard of care at 16 weeks from baseline.
The secondary aim of this study is exploratory and will compare daily healthy meals or produce box versus matched controls in improving chronic disease markers:This aim tests the hypothesis that receiving daily healthy meals will result in greater improvement in hbA1c and blood pressure compared to receiving a produce box or standard of care box at 16 weeks, six months, and 12 months from baseline.This aim tests the hypothesis that receiving either daily healthy meals or a produce box will result in greater improvement in weight, hbA1c and blood pressure compared to standard of care at 16 weeks, six months, and 12 months from baseline.
To assess whether receiving daily healthy meals or a produce box in conjunction with nutrition counseling and education results in improvement in food insecurity, diet quality, depression, self-efficacy for healthy eating and healthy weight, and self-efficacy for chronic disease management from baseline to 16 weeks.

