### Study design

This study is a parallel-arm quasi-randomized control trial with nonequivalent matched controls, which will be conducted between January 2022 and December 2023. Seventy adult patients recruited from our ambulatory practice will be randomly assigned to receive either: i) daily healthy frozen meals or ii) a weekly produce box and recipes for 15 weeks. Each study arm will comprise 35 patients with a documented diagnosis of obesity (body mass index [BMI] equal to or greater than 30kg/m^2^) and one or more of the following conditions: pre-type 2 diabetes/type 2 diabetes or hypertension. Participants will complete an in-person baseline visit and a follow-up visit at 16 weeks from baseline, and their medical charts will be reviewed for trends in these biomarkers at six months and 12 months from baseline. Healthy meals or a produce box will be shipped to the home address of participants once a week. Healthy meals provided in the study are low-sodium and diabetic-friendly ready-to-heat and serve breakfast, lunch, and dinner items. The produce box provided in the study will comprise fresh vegetables and fruits. For participants receiving a produce box, recipes utilizing items contained in the box will be available at the vendor’s website.

All participants will complete one individual medical nutrition therapy session via phone with a dietitian. The individual medical nutrition therapy appointment will occur within two weeks of enrollment in the study. A total of four nutrition and health videos, each under 10 minutes in length, will be available for participants to view between weeks 3 and 15 of the study. The complete study procedures are outlined in Table 1. Participants will be required to view the videos on healthy eating and weight loss and, as applicable to their health status, videos on type 2 diabetes and hypertension (see Table 2). The Healthie application (https://www.gethealthie.com/?afmc=a46i) will be utilized for nutrition education programming. Through the Healthie application, participants will receive automated text and/or email reminders to view educational videos. This feature is designed to drive compliance and completion of the nutrition education component. A report will be generated to provide completion percentage and other details based on participant engagement. The Healthie application is compliant with the US Health Insurance Portability and Accountability Act.

**Table 1. tbl1:** Schedule of study activities

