Study activity	Baseline visit (W0)	Week 2 (W0–W2)	Week 3 – 15 (W3–W15)	Week 16 visit (W16 ± 7 days)	6 months	12 months
Informed consent process	x					
Anthropometric data (weight, height, and blood pressure)	x			x	x	x
HbA1c	x			x	x	x
Completion of study questionnaires	x			x		
Individual nutrition counseling session		x				
Nutrition education videos			x			

**Table 2. tbl2:** Expected viewership of nutrition education videos

	Video title			
	Introduction to nutrition	Nutrition and weight loss	Nutrition and diabetes	Nutrition and hypertension
All participants	x	x		
Participants with pre-/type 2 diabetes			x	
Participants with hypertension				x
Participants with pre-/type 2 diabetes AND hypertension			x	

The control group will comprise 70 participants matched to intervention group participants based on BMI, diagnosis of pre-type 2 diabetes/type 2 diabetes, and/or hypertension. Control group participants will be identified from the electronic medical record, Epic^®^, after enrollment of all intervention arm participants has been completed. A flow chart of participant recruitment and completion of study activities is shown in Figure 1. Our study protocol adheres to the SPIRIT guidelines for clinical trial protocols (Chan *et al.*, 2013) and is registered on ClinicalTrials.gov with identifier NCT05174078.

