### Sample size determination

Similar past research conducted in the US (Berkowitz, Delahanty, *et al.*, 2019) was used to estimate a baseline weight of 92 ± 16 kg for the study population. In order to estimate the effect size of weight loss potential in the intervention groups, the CDC healthy eating standard range of 1 to 2 pounds weight loss per week was used. The estimate for weight loss in the healthy meals group was 2 pounds per week over 15 weeks, and the estimate weight loss for the produce group was 1 pound per week for 15 weeks. It was assumed that there would be no weight change in the matched controls (standard of care) group. A one-way AONVA sample size calculation was performed using the following parameters: mean weight (kg) [matched controls 92, healthy meals 78.4, Produce 85.2], standard deviation 16 for all groups, 0.80 power, and 0.05 alpha. This yielded a sample size of 28 per group. We assume a 10% attrition rate, bringing the sample size to 35 per group.

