### Data analysis

The independent variables in this study are study arm (healthy meals, produce box, and matched controls [standard of care]), nutrition counseling and education, and time (pre-intervention, 16 weeks, six months and 12 months). The primary dependent variable (outcome) is absolute weight change at 16 weeks between groups. The secondary dependent variables (outcomes) are as follows: i) absolute weight change at six months and 12 months from baseline; ii) change in hbA1c, dosage, and number of diabetes medications; iii) change in dosage and number of blood pressure medications, and; iv) change in numeric rating from baseline to 16 weeks for food insecurity, diet quality, depression as well as self-efficacy for health eating, healthy weight, and chronic disease management. A final outcome of interest is satisfaction rating for the interventions provided in the study, measured using a non-validated questionnaire developed for this study.

Descriptive statistics will be calculated for demographic data and for each dependent variable by group, nutrition counseling and education, and time. Separate repeated-measures ANOVAs will be conducted for each dependent variable with the between subjects factor group (healthy meals, produce box, and matched controls) and the within subjects factor time (pre-intervention and 16 weeks). *Post hoc* testing will be conducted as appropriate. Effect sizes will be calculated between pre-intervention and 16 weeks to capture the changes from pre- to post-intervention. Missing data will be analyzed using an intention-to-treat strategy. Statistical analysis will be performed by a biostatistician using SAS statistical software. The biostatistician will be blinded to the intervention for each group to eliminate potential bias during data analysis.

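### The standard repeated-measures ANOVA lets 70 chart controls supply half the error degrees of freedom for the randomised meals-versus-produce contrast; group-specific variances would keep them out at little cost

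*Protocol article*

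**What the plan says.** The Data analysis section of the protocol article defines the outcome: "The primary dependent variable (outcome) is absolute weight change at 16 weeks between groups". The model is given as "Separate repeated-measures ANOVAs will be conducted for each dependent variable with the between subjects factor group (healthy meals, produce box, and matched controls"), crossed with "the within subjects factor time (pre-intervention and 16 weeks"). On follow-up comparisons it says only that post hoc "testing will be conducted as appropriate". It names no covariance structure, variance check or contrast method.

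The Study aims section makes meals versus produce part of a primary hypothesis: "receiving daily healthy meals will result in greater absolute weight loss compared to receiving a produce box or standard of care at 16 weeks from" … Under Study design, "Each study arm will comprise 35 patients with a documented diagnosis of obesity", and "The control group will comprise 70 participants matched to intervention group participants based on BMI" and diagnoses. Controls are found in the electronic medical record, while the food arms are weighed at study visits. Sample size determination uses "standard deviation 16 for all groups", with planning means of 92 kg (controls), 85.2 kg (produce) and 78.4 kg (meals).

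**The concern.** With two time points, the group-by-time test is a one-way ANOVA on weight change. The classical version estimates one error variance from all three groups and uses it for every contrast. That is harmless if weight change varies equally in all groups, but here nothing supports equal spread. The control weights come from a different measurement process, and the expected losses are 0, 6.8 and 13.6 kg.

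The randomised comparison is the one most exposed. Its standard error should reflect the spread of change in the two food arms. Under pooling, about half of it is set by retrospective records of people who were never randomised. If those records vary less than the food arms, the interval for meals versus produce is too narrow. If they vary more, it is too wide and the trial's best evidence is diluted. This would remain even if the controls were perfectly comparable, so it is separate from confounding.

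**Working it through.** **1. The plan's own figure.** One-way ANOVA, means 92, 78.4 and 85.2, common SD 16, alpha 0.05, noncentral F with 2 and 3n − 3 degrees of freedom: n = 28 gives power 0.805 and n = 27 gives 0.789. The stated 28 per group is reproduced. The SD of 16 is the spread of baseline body weight. It shows an equal-SD premise in planning but says nothing about the spread of change. The planned 35 per food arm is taken as stated.

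**2. Weight of the controls in the error term.** Error degrees of freedom are 34 + 34 + 69 = 137, and 69/137 = 50% come from controls. The expected pooled variance is

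E(MSE) = (34·s_M² + 34·s_P² + 69·s_C²)/137,

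where s_M, s_P and s_C are the SDs of change for meals, produce and control.

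**3. Effect on meals versus produce.** The pooled SE uses E(MSE)·(1/35 + 1/35). The true variance is s_M²/35 + s_P²/35. With equal food-arm SDs at r times the control SD,

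pooled SE / true SE = √[(68r² + 69)/(137r²)].

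At r = 1.25: √(175.25/214.06) = 0.905. The true error is roughly 2·[1 − Φ(1.977 × ratio)], where 1.977 is the t critical value on 137 degrees of freedom. Simulation gives the figures below, good to about 0.1 percentage points. All SDs are assumptions, since the article gives none.

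| Food SD / control SD (kg) | r | Pooled SE / true SE | True error of nominal 5% test |
|---|---|---|---|
| 5 / 5 | 1.00 | 1.00 | 5.0% |
| 5 / 4 | 1.25 | 0.91 | 7.5% |
| 6 / 4 | 1.50 | 0.85 | 9.5% |
| 6 / 3 | 2.00 | 0.79 | 12.1% |
| 5 / 6 | 0.83 | 1.11 | 3.1% |
| 5 / 7 | 0.71 | 1.22 | 1.7% |
| 4 / 6 | 0.67 | 1.28 | 1.3% |

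If the food arms lose people and end at 28 each with 70 controls, the controls' share rises to 69/123 = 56%. The error is then 7.9% at r = 1.25, 13.7% at r = 2 and 1.1% at r = 0.67.

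**4. If spread grows with weight lost.** Take SD = √[4² + (CV × loss)²] with CV 25% to 50% (assumed), and set the groups being compared to equal loss, as a null hypothesis requires.

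- Meals versus produce, controls at 0 kg: about 6% to 8% if both food arms lose 6.8 kg, 7% to 10% at 10.2 kg, and 8% to 12% at 13.6 kg.
- Meals versus control, both at 0 kg and produce at 6.8 kg: about 4.5% down to 3.3%, so conservative.
- Omnibus test: all losses are equal, so all spreads are equal, and the error is 5%.

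**5. Does a prior significant F test protect the contrast?** When all three groups are truly equal, running contrasts only after a significant F lowers the error to about 3% to 7%. The plan expects controls to differ, however. With both food arms losing 6.8 kg, or half that, and controls at 0, the F test is almost always significant. The gated meals-versus-produce error is then 7.6% (5/4), 9.6% (6/4) and 12.2% (6/3).

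**6. After the change.** Welch contrasts at 35/35/70 and 28/28/70 give 4.9% to 5.1% at every ratio from 0.67 to 2.

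**The case against.** The strongest objection is that the article never says the variance is common. A repeated-measures model in SAS can allow group-specific variances, and covariance structure is commonly left to an analysis plan, which is not shown. This stands in part, and it is why the point is phrased about the standard form of the method. But the article does name a method, its default pools across randomised and non-randomised groups, and nothing else in the text departs from that default.

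A reader might infer more: that error bars are wrong in a way that favours meals, or that the meals-versus-control and omnibus tests are also inflated. The documents support neither. They give no SD of change, and chart weights could well be noisier than study-visit weights, which makes meals versus produce conservative. If spread grows with loss, step 4 shows that the omnibus test keeps 5% and meals versus control is conservative. Inflation there would need the food arms to vary more than controls without differing in mean, which nothing in the article indicates.

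It is also fair to say that the planned effects would survive. With assumed SDs of 7.9 (meals) and 5.2 (produce), the planned 6.8 kg difference gives t = 6.8/√(7.9²/35 + 5.2²/35), about 4.2. An SE change of 10% to 20% would not reverse that. It matters if the observed difference is smaller.

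**Conclusion.** The point holds in a limited, conditional form. In its standard form the named ANOVA lets the chart controls supply half the error degrees of freedom for the randomised contrast, and the article gives no basis for assuming that they share its variance. The true error of the nominal 5% meals-versus-produce test is about 7.5% to 12% for assumed food-to-control SD ratios of 1.25 to 2, and about 3% to 1% for ratios of 0.83 to 0.67. Both ranges assume 35/35/70, equal SDs in the two food arms, normally distributed change and unadjusted contrasts. Which range applies cannot be told from the documents. The same change removes the problem either way, so this is a cheap improvement rather than a flaw that undermines the trial.

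**What to change.** In Data analysis, specify a model for weight at baseline and 16 weeks with a separate residual variance (or covariance matrix) for each group, for example SAS PROC MIXED with REPEATED / GROUP=arm and Kenward-Roger or Satterthwaite degrees of freedom. Welch contrasts on weight change would serve equally. The meals-versus-produce standard error then comes from the two randomised arms only. Report the SD of weight change per group.

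The cost is one SAS option and a sentence. If the variances are in fact equal, degrees of freedom for meals versus produce drop from 137 to about 68. The t critical value rises from 1.977 to 1.995, and the interval widens by about 1% (1.995/1.977 = 1.009). Where the pooled error was too small, the interval becomes wider, as it should.

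### The stated ANOVA takes no account of how controls were matched, so comparisons with standard of care are somewhat conservative if weight change is correlated within matched sets (minor)

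*Protocol article*

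**What the plan says.** All of this is in the protocol article.

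- **Selection of controls (Study design).** "The control group will comprise 70 participants matched to intervention group participants based on BMI", and also on pre-diabetes or type 2 diabetes and/or hypertension. They are taken from the electronic record after enrolment to the food arms is complete. No matching ratio, tolerance or pairing rule is given.
- **Arm size (Study design).** "Each study arm will comprise 35 patients", so 70 participants receive food and 70 are controls.
- **Primary outcome (Data analysis).** "The primary dependent variable (outcome) is absolute weight change at 16 weeks between groups".
- **Model (Data analysis).** Repeated-measures ANOVAs "with the between subjects factor group (healthy meals, produce box, and matched controls) and the within subjects factor time (pre-intervention and 16 weeks"). Time is the only within-subjects factor. No matched-set term and no matching covariate is named.
- **Sample size (Sample size determination).** "A one-way AONVA sample size calculation was performed using the following parameters". The inputs are group means of 92 kg (controls), 78.4 kg (meals) and 85.2 kg (produce), a common SD of 16 kg, 80% power and a 5% significance level. This is a calculation for independent groups.

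**The concern.** Matching makes the control group resemble the food arms on factors that may predict the outcome. As far as they do, the outcomes of a participant and the matched control are positively correlated, and the difference between group means varies less than it would between unrelated groups. An analysis that treats the groups as unrelated leaves that covariance in the error term. Its estimate is not biased by this, but its standard error is too large, its confidence intervals are too wide and its true type I error is below 0.05.

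Both primary hypotheses in Study aims include a comparison with standard of care, so the contrasts concerned are central. Strengths and limitations names the small sample as a weakness, so precision is worth keeping. This is a separate matter from residual confounding: it would remain even if the matching balanced the groups perfectly.

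**Working it through.** **Inputs.** From the document: 35 meals, 35 produce, 70 controls; means 92, 78.4 and 85.2 kg; SD 16 kg; alpha 0.05. Inferred: one control per participant, from 70 and 70. Assumed: rho, the within-set correlation of 16-week weight change, shown from 0 to 0.5.

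**1. The plan's own figure.** For three equal independent groups, the grand mean is 85.2 and the squared deviations sum to 2 × 6.8² = 92.48. The noncentrality is n × 92.48 / 16², which is 10.115 at n = 28. The F test then has 80.5% power (78.9% at n = 27). The stated 28 per group reproduces and uses no matching.

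**2. What the ANOVA tests.** With two time points, the group-by-time test is a one-way ANOVA on the change score. The relevant correlation is therefore that of weight change, not of weight.

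**3. One food arm against all 70 controls.** Let s be the SD of change. Half of the controls are matched to this arm.

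- Nominal variance: s²(1/35 + 1/70) = 3s²/70.
- True variance of the same mean difference: s²(1/35 + 1/70 − 2·rho/70) = (3 − 2·rho)s²/70.
- SE ratio k = √[3/(3 − 2·rho)]. True two-sided type I error = 2[1 − Φ(1.96k)].

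**4. Both food arms pooled (70) against 70 controls.** The ratio is 1/√(1 − rho), with type I error from the same formula.

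| rho (assumed) | One arm: SE ratio | One arm: type I error | Pooled: SE ratio | Pooled: type I error |
|---|---|---|---|---|
| 0 | 1.000 | 0.050 | 1.000 | 0.050 |
| 0.1 | 1.035 | 0.042 | 1.054 | 0.039 |
| 0.2 | 1.074 | 0.035 | 1.118 | 0.028 |
| 0.3 | 1.118 | 0.028 | 1.195 | 0.019 |
| 0.5 | 1.225 | 0.016 | 1.414 | 0.006 |

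The SD cancels from every entry.

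**5. How large rho could be.** In a change score the shared baseline level drops out. Rho is positive only as far as the matching factors predict change. In a simulation of 70 pairs whose baseline values correlate 0.95 (an assumption), baseline explaining 0%, 5%, 10% or 30% of the variance in change gave SE ratios of 1.00, 1.03, 1.05 and 1.18 and type I errors of 4.9%, 4.3%, 4.0% and 2.0%. In that set-up rho is 0.95 times the share explained. Rho of 0.2 needs about 21% explained (0.2/0.95), and rho of 0.5 needs about 53%.

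**The case against.** The strongest reply has four parts.

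- **No promised power is lost.** The 80% was computed for independent groups, and any error here is conservative. This stands. The loss is only relative to a better analysis.
- **Rho may be near zero.** Matching is on BMI and diagnosis, and the outcome is change. This also stands: at rho up to 0.1 the one-arm standard error is at most 3.5% too large.
- **Individual pairing is not stated.** Equal numbers suggest 1:1, but group-level matching fits the text as well, and then there is no set to index. This stands, and it is why the main fix is adjustment for the matching factors, which serves either form.
- **Model terms may be left to the analysis plan.** This stands only in part. The article does not leave the model open. It names the between- and within-subjects factors, and what it names does not reflect the design.

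A reader might infer a large loss of power by putting the 16 kg SD into the produce versus control contrast of 6.8 kg: about 54–55% ignoring matching against 77% with a matched-set effect at rho 0.5. The document does not support that. It gives 16 kg as the spread of body weight, while the test is on change. Take a change SD of 10 kg instead (an assumption), with variance (3 − 2·rho − rho²)s²/70 for the matched-set estimator. At rho 0.5 power is then Φ[(6.8 − 1.96 × 2.070)/1.690] = 94.8% ignoring matching and Φ[6.8/1.581 − 1.96] = 99.0% with it, a gain of about 4 points. At a change SD of 7 kg both exceed 99%.

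**Conclusion.** The point holds as a conditional and minor one. Controls are selected by matching, and the stated ANOVA reflects this neither through a set term nor through the matching factors. If weight change is positively correlated within sets, contrasts with standard of care have standard errors that are too large. For a single arm the excess is 3.5% at rho 0.1 and 12% at rho 0.3, with type I error of 0.042 and 0.028. At rho 0 there is no effect.

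The figures rest on 1:1 pairing, which is inferred, and on rho, which the document does not give. For weight change rho is probably low. It would be wrong to conclude that standard errors are certainly too large, that the planned 80% power is reduced, or that false positives are inflated; the error runs the other way. The comparison of meals with produce is little affected.

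**What to change.** Compare 16-week change between groups in a model that includes the matching factors: baseline BMI or weight, diabetes status and hypertension. These are already collected for participants and are needed to select the controls. This works whether matching is individual or at group level.

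If controls are individually paired, record the set identifier at selection and add a random matched-set effect on change (in a model for weight at both times, a set-by-time effect). This keeps sets with one missing member and uses all 70 controls for each arm. A paired t-test of each arm against its own 35 controls is a poor substitute: its variance is (4 − 4·rho)s²/70, which exceeds even the unmatched 3s²/70 unless rho is above 0.25.

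The cost is a change of wording, a few extra model terms and, where pairs exist, one identifier column. No patients or measurements are added. If rho is near zero, little is gained.
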